**Methods/design:**

Early stage cancer survivors will be recruited via the research arm of a not-for-profit clinical research unit and randomised to an intervention (iCBT) group or a ‘treatment as usual’ (TAU) control group. The minimum sample size for each group is 45 people (assuming effect size > 0.6, power of 80%, and alpha at .05), but 10% more will be recruited to account for attrition. A solitary or cumulative diagnosis(es) of Major Depressive Episode (current), Generalised Anxiety Disorder, Illness Anxiety Disorder, Panic Disorder, Agoraphobia, and/or Adjustment disorder will be determined using modules from the Anxiety Disorders Interview Schedule for DSM-5. Depression and anxiety levels with be measured via the total score of the Hospital Anxiety and Depression scale (HADS-T), the primary outcome measure. Secondary measures will include the Kessler 10 to measure general distress, the Fear of Cancer Recurrence Inventory (FCRI) to measure the specific fear of cancer recurrence and the Functional Assessment of Cancer Therapy, General Version 4 (FACT-G) for self-report of physical, social, emotional and functional well-being. iCBT participants will complete the measures before lessons 1 and 5, at post-treatment and at 3-month follow-up. The TAU group will complete similar measures at weeks 1, 8 and 16 of the waiting period. Program efficacy will be determined using intent-to-treat mixed models. Maintenance of gains will be assessed at 3-month follow-up. Mediation analyses using PROCESS will be used to examine the association between change in depressive and anxious symptoms over time and changes in FCRI and FACT-G QOL in separate analysis.

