### Recruitment

Participants will be recruited through flyers, internet social media advertising, cancer support groups and cancer research email listings. Applicants will first complete online screening questionaries about depressive and anxious symptoms and their demographic details will be collected. Inclusion criteria to proceed to the phone interview are as follows; resident of Australia; ≥ 18 years of age, a total score of ≥ 6 on the Hospital Anxiety and Depression scale (HADS-T) and a self-report of early stage cancer or cancer survivorship. This HADS-T cut-off was chosen as it will allow identification of 95% of cases [29, 30]. Applicants will also be asked a number of questions related to the exclusion criteria (see below) and will not proceed to phone interview if they endorse them. Applicants also complete the Alcohol Use Disorders Identification Test Consumption (AUDIT-C) questions but are not excluded on the basis of the results at this stage [31, 32]. See Fig. 1 for a participant flow chart.

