### Trial design and blinding

The trial is a stratified randomised controlled superiority trial with parallel arms using a 1:1 allocation ratio. It is stratified according to ‘active treatment’ and ‘post treatment’. The ‘active treatment’ group are those who are at least six weeks from their initial cancer diagnosis, and are currently undertaking major cancer treatments such as chemotherapy or radiotherapy. The ‘post treatment’ group are those who have completed their primary treatment for cancer [34] with no upper timeframe. Experimenters and Participants will be aware of their group allocation but as all measures are self-report blinded assessors will not be required.

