### Randomisation

Accepted participants will be stratified according to their phase in their cancer experience into the ‘active treatment’ group and ‘post-treatment’ group as described earlier. Thereafter, they will be randomised based on an allocation sequence generated by an independent person not involved in the study via a true randomisation process (www.random.org). Numbers corresponding to treatment group (1 = iCBT) or the treatment as usual group (2 = TAU) will be placed in sealed opaque envelopes bearing the sequential order number to ensure participant allocation based on the pre-determined randomisation sequence. A member of the research team will open the envelope after the diagnostic interview.

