### Trial procedure

Figure 1: Participant Flow Chart details the time line for participants in the study. Once randomised, participants will be allocated to either the iCBT arm or the TAU arm. Over the sixteen week period, both groups undertake the same set of measures three times, the start, mid-point and end of the intervention. In the iCBT group, these times will vary according to when the participant undertakes the specific lesson; whereas for the TAU group, the questionnaires are according to specific times (i.e. weeks since commencement of group). Administration time points for measures are contained in Table 1. Baseline records of psychotropic medications and whether they are accessing psychological support will be captured for participants in both groups. Participants will be asked to inform the research team if any of their current interventions change.

**Table 1 Tab1:** Administration time points for questionnaires used in the RCT

Measure	Pre-treatment^a^	Before each lesson^b^	Mid –treatment^c^	Post-treatment^d^	3-month follow-up^b^
HADS-T	♦		♦	♦	♦
K-10	♦	♦	♦	♦	♦
PHQ9-Q9	♦		♦	♦	♦
BDI-II Item 9	♦		♦	♦	♦
FCRI	♦		♦	♦	♦
FACT-G	♦		♦	♦	♦
CEQ	♦			♦	
ADIS	♦				♦

*HADS-T* Hospital Anxiety and Depression Scale,Total score, *K-10* Kessler-10 Psychological Distress Scale, *PHQ9-Q9* Patient Health Questionnaire 9-itme scale, Question 9, *BDI-II Item 9* Beck Depression Inventory-II, Item 9, *FCRI* Fear of Cancer Recurrence Inventory, *FACT-G* Functional Assessment of Cancer Therapy – General, *CEQ* Credibility and Expectancy/Satisfaction Questionnaire, *ADIS* Anxiety Disorders Interview Schedule for DSM-5

^a^iCBT group pre Lesson 1; TAU group at week 1 (Baseline)

^b^iCBT group only

^c^iCBT group pre Lesson 5; TAU group at week 8

^d^ iCBT group post Lesson 8; TAU group at week 16 (End)

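### The scheduled baseline HADS-T is self-rated after participants learn their arm, so the reference for pre-to-post contrasts can be affected by allocation

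*Protocol article*

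**What the plan says.** All references are to the protocol article.

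- **Recruitment:** applicants complete online screening, which requires "a total score of ≥ 6 on the Hospital Anxiety and Depression scale (HADS-T)". This score precedes randomisation and its stated use is eligibility.
- **Randomisation:** "A member of the research team will open the envelope after the diagnostic interview".
- **Trial design and blinding:** "Experimenters and Participants will be aware of their group allocation". The same sentence adds that "as all measures are self-report blinded assessors will not be required".
- **Trial procedure:** "Once randomised, participants will be allocated to either the iCBT arm or the TAU arm"; the three sets of measures are then described as falling within the sixteen weeks. The assessment clocks differ: "In the iCBT group, these times will vary according to when the participant undertakes the specific lesson", whereas TAU is assessed at fixed weeks.
- **Table 1, note a:** pre-treatment means "iCBT group pre Lesson 1; TAU group at week 1 (Baseline)".
- **Abstract, Methods/design:** agrees with the table: "iCBT participants will complete the measures before lessons 1 and 5, at post-treatment and at 3-month follow-up".
- **Primary outcome measure:** the endpoint is HADS-T severity at post-treatment.
- **Statistical methods:** intent-to-treat mixed models fitted by REML, with significant effects followed by contrasts of mean pre-treatment against mean post-treatment scores. The arms are also tested for differences on pre-treatment measurements, and drop-outs are compared with completers on baseline measures.

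**The concern.** A baseline is a clean reference only if allocation cannot influence it. Here one arm rates its distress just before starting treatment and the other just after learning that it will wait 16 weeks. Relief, hope or disappointment could move the ratings differently in the two arms. The planned test of pre-treatment differences could not separate such a reaction from chance imbalance.

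A second issue follows from the two clocks. Notes a, c and d of Table 1 tie the iCBT pre, mid and post measures to Lessons 1, 5 and 8. A TAU participant is approached at weeks 1, 8 and 16 whatever their engagement. An iCBT participant who never engages may therefore have no scheduled HADS-T at all. Such a person would add nothing to the mixed model and would have no scheduled baseline for the planned drop-out comparison.

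**Working it through.** **1. Order of events.** Online screening with HADS-T; telephone interview; electronic consent before enrolment; envelope opened after the interview; arm known; then pre-Lesson 1 (iCBT) or week 1 (TAU). A time point defined differently for each arm can only come after the arm is known. Note a is not literal for every row of Table 1: it also covers the ADIS, which is done at the interview before the envelope is opened. For HADS-T, the abstract and the Trial procedure text both support the note.

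**2. The plan's sample size.** Inputs from Statistical methods: standardised effect 0.6, power 80%. Two-sided alpha 0.05 is taken from the abstract's .05; sidedness is not stated.

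n per group = 2 × (1.960 + 0.842)² / 0.6² = 43.6, so 44, which reproduces the plan. The t-test version gives 44.6, so 45, as in the abstract. Only a standardised between-group effect enters, so moving the baseline does not change n.

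**3. How a shift is transmitted.** Let s be the between-arm shift at baseline caused by knowing the arm, in SD units, and r the pre-post correlation (equal SDs).

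- Change or time-by-group contrast: bias = s
- Baseline-adjusted contrast: bias = r × s
- Unadjusted post-treatment comparison: bias = 0

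The values of s and r below are assumptions; the article gives neither.

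| s | s / 0.6 | Adjusted bias, r = 0.5 | Adjusted bias, r = 0.7 |
|---|---|---|---|
| 0.1 | 17% | 0.05 | 0.07 |
| 0.2 | 33% | 0.10 | 0.14 |

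**4. Effect on a change contrast.** With 44 per group and unit SD of the contrast, SE = √(2/44) = 0.213. For a true effect of 0.6:

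| s | Against iCBT: effect, power | For iCBT: effect, power |
|---|---|---|
| 0.1 | 0.5, 65% | 0.7, 91% |
| 0.2 | 0.4, 47% | 0.8, 96% |

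The planned power is 80%.

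With no true effect, the SD of change is √(2(1 − r)). The two-sided error, nominally 5%, becomes 7.6% (s = 0.1) or 15.5% (s = 0.2) with r = 0.5, and 9.3% or 22.8% with r = 0.7.

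**5. Non-starters.** Suppose 10% or 20% of the 50 iCBT participants provide no HADS-T (assumed rates). Then 45 or 40 are compared with 50, and power for 0.6 is 83% or 81%. The possible harm is selection in one arm, not loss of power.

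**The case against.** The primary endpoint is HADS-T at post-treatment, not change, and the article does not list the model terms. A reader might infer that any baseline shift biases the treatment effect one-for-one. The documents do not support that as a general rule: step 3 shows it holds only for change or time-by-group contrasts. This objection stands and limits the point.

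A reader might also infer that baseline is missing for everyone who never opens Lesson 1, and that intent-to-treat is therefore broken. Neither is stated. The questionnaire comes before the lesson, so someone can complete it and go no further. A mixed model keeps anyone with at least one observed score, and TAU participants can also miss week 1. Handling of non-starters may be set out in an analysis plan that is not shown. What remains is a possibility created by the lesson-driven clock.

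The shift itself is undemonstrated. Disappointment raising TAU ratings, or hope lowering iCBT ratings, would make a pre-to-post contrast less favourable to iCBT, which is conservative for a superiority claim. The opposite shift would favour iCBT. The article does not settle which applies.

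Finally, the participant flow figure, said to give the time line, is not available here, and the article does not rule out using the screening HADS-T as a covariate. These points temper confidence but do not displace the sequence given consistently in the text, Table 1 and the abstract.

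**Conclusion.** The point holds in limited form. The article schedules the pre-treatment HADS-T after open allocation, in a trial where all outcomes are self-rated, and uses it as the reference for the pre-to-post contrasts. Those contrasts can therefore be affected by allocation. The primary post-treatment comparison is exposed only to the extent that the model uses this baseline.

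Size and direction are unknown. The 17% to 33% of the planned effect rests on an assumed shift of 0.1 to 0.2 SD passing in full into a change contrast; with adjustment and an assumed correlation of 0.5 it halves. No rate of non-starting is given, so the asymmetry in missing data is a risk and not an established loss. The documents do not support a claim that the trial's result will be biased in favour of iCBT, or that its intent-to-treat analysis fails. The change is worth making because it removes a possible bias at little cost.

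**What to change.** 1. **Future participants:** have them complete the self-report part of the Table 1 pre-treatment battery online after consent and before the envelope is opened.
2. **Those already randomised:** use the pre-randomisation screening HADS-T as the baseline covariate in the primary model. Do not use the post-allocation score as the reference.
3. **Analysis set:** state that every randomised participant is kept in the analysis by randomised arm, whether or not Lesson 1 was started, and say how those with no scheduled HADS-T are handled.

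The cost is reordering one online questionnaire and a few sentences of analysis wording; sample size is unaffected. The downsides are a slightly longer gap between baseline and Lesson 1, and two baseline regimes within one trial, since enrolment began on 1 March 2016. For HADS-T the second can be avoided by using the screening score as covariate for everyone, because screening requires it of all applicants. For FCRI and FACT-G no screening measurement is described, so those already enrolled would keep a post-allocation baseline on these outcomes. The report should say so.

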### Description of the interventions

#### Internet delivered CBT (iCBT), the ‘iCanADAPT Early’ program group

The ‘iCanADAPT Early’ Program is a self-managed, 16 week online cognitive-behavioural intervention consisting of eight lessons involving general CBT skills and then cancer-specific CBT skills. Content is presented in the form of an illustrated comic-based storyboard in which two animated characters gain mastery over their anxiety and depressive symptoms with the help of a clinician. The female character is currently undergoing cancer treatment and tackling clinical levels of depression, while the male character is post-treatment with predominant anxiety symptoms. The participant follows both characters journeys to recovery across the 8 lessons. The *title*, and expansion of the main focus of each lesson are in Table 2: Course overview.

**Table 2 Tab2:** Course overview

Lesson 1 - *Learning about Depression & Anxiety* Psycho-education about depression and anxiety, including their prevalence in cancer, psycho-education about the CBT cycle and the flight or fight response. Introduction to rumination and worry and good sleep hygiene. Skills of relaxation and progressive muscle relaxation. Lesson 2 - *Identifying and Tackling Thoughts* Key cognitive therapy skills including cognitive monitoring, recognising distorted cognitive styles, and later cognitive restructuring. Examples of each skill in use. Lesson 3 - *Tackling Unhelpful Behaviours* Key behavioural activation skills including tackling the low activity cycle, daily activity scheduling and the role of physical activity in improving general health. Additional skills relating to structured problem solving and assertive communication skills. Lesson 4 - *Helpful Coping* Further cognitive skills including worry-Free Zones and challenging mega-cognitions. Expanded attention to CBT strategies to tackle sleep difficulties. An introduction to mindfulness and related extra resources. Lesson 5 - *Adjusting to Change* Assessment of one’s personal values and goals. The need to pace physical activity. The use of CBT to tackle the impact of physical health (and/or treatment) symptoms on emotional wellbeing. Lesson 6 - *Tackling Avoidance* Introduction to avoidance and the rationale for combatting avoidance using graded exposure and exposure stepladders. Numerous examples of confronting avoidance (both in cancer and non-cancer settings) are intertwined to allow generalisation. Lesson 7 - *Mastering Your Skills* A guide to potential pitfalls that people encounter when trying to master CBT skills, in particular that of exposure work. An introduction to imaginal exposure. Lesson 8 - *Staying Well in the Long Term and Getting Even Better* Relapse prevention planning and an overview of the skills learned.	

At the end of each lesson, participants download a Lesson Summary which expands on the cartoon storyboard and provides a structured outline of the information. It also encourages participants to complete homework activities and review the lesson content at a later date. Extra resources are provided to participants and include worksheets examples.

## Clinician guidance for iCBT group

Each participant’s scores and engagement are monitored over the course of the working week. At minimum, individual email contact is made to each participant after the completion of Lesson 1 and Lesson 2. Thereafter, further email and/or phone contact will be made to participants depending on their needs. Typical reasons for clinician contact include an increase in distress scores, a participant question relating to content or a participant taking an unexplained break from logging in. Participants will have the opportunity to volunteer feedback about their most recent lesson/week(s) before each subsequent lesson and these responses will occasionally prompt clinician contact.

### Treatment as usual (TAU) group

Participants allocated to the TAU group may access their local general practitioner, community or cancer centre (mental) health services during the course of their waiting period.

## Clinician guidance for TAU group

Each participant’s questionnaire responses (week 1, 8 and 16) are reviewed. A generic email is sent from the Virtual Clinic system to thank participants for completing their questionnaire. Clinician contact will only be made if there are unexpected high HADS, or K-10 scores, or significant change from the scores previously obtained. Upon completion of the 16-week waiting period, and upon completion of the final set of TAU questions, the participants will transition to iCBT and then receive clinician guidance during their iCBT program as described above.

### Measures

#### Primary outcome measure

### Hospital anxiety and depression scale, total score (HADS-T)

The primary endpoint is anxiety and depression severity at post treatment as measured by the Hospital Anxiety and Depression Scale Total score (HADS-T) [35]. The HADS was developed as an outcome measure to assess anxiety and depression that avoids reliance on the measurement of somatic symptoms (e.g., fatigue, or insomnia) that may be experienced by people with cancer as part of the presenting illness. HADS-T is a fourteen item self-report questionnaire divided into two sub-scales, HADS-D, depression subscale and HADS-A, an anxiety subscale. The HADS-T is the total HADS score and is the combined score of the depressive and anxiety sub-scales. High scores indicate greater morbidity. This validated measure is widely used in clinical settings and has been validated in cancer patients [29].

### Secondary outcome measures

**Kessler-10 Psychological Distress Scale** (K10) [36]: The K10 contains 10 items ranked on a 5-point scale designed to measure non-specific psychological distress. High scores indicate higher distress. The K10 has been validated in a mixed cancer-type population [37]. Furthermore, the K10 is a quickly administered online tool and is advantageous for monitoring iCBT patients [38]. For the current study, the time frame was modified to assess psychological distress in the past 2 weeks rather than the past 30 days.

**Patient Health Questionnaire 9-item scale, Question 9** (PHQ9-Q9 [39]) **and Beck Depression Inventory-II, Item 9** (BDI-II,i9), [40]: The HADS-T and the K-10 do not contain questions regarding either a passive death wish or suicidal ideation. Therefore, these two screening questions for ‘better off dead’ thoughts and suicidality are included in the assessment of patients, and score changes are automatically reported. These questions allow the monitoring clinician to make contact with participants should changes occur.

**Fear of Cancer Recurrence Inventory** (FCRI) [41]: The 42-item Fear of Cancer Recurrence Inventory was chosen as it is an aggregate score of seven sub-scales ranging from triggers to level of insight into the problem. The FCRI severity subscale is reported to be the most informative regarding a patient’s level of fear [42]. High scores indicate greater fear of cancer recurrence. Possible associations between the FCRI subscale scores and the clinical diagnoses via the ADIS, and/or other determinants [43] including treatment response, will be assessed.

**Functional Assessment of Cancer Therapy – General** (FACT-G, version 4) [44]: The FACT-G is a 33-item general cancer quality-of-life measure. FACT-G has been established as a valid and reliable measure [45]. FACT-G was chosen over other quality of life measures as it has scales looking at the impact of symptoms on relationships and supports [46].

**Credibility and Expectancy/Satisfaction Questionnaire** (CEQ) [47]: At baseline, participants will complete two treatment expectancy questions: (1) “At this point, how logical does the program offered to you seem?” (0 = “Not at all logical”; 9 = “Very logical”) and (2) “At this point, how successfully do you think this treatment will be in reducing your depression and anxiety symptoms?” (0 = “Not at all useful”; 4 = “Very useful”). Following the combined intervention, participants will also rate treatment satisfaction: “How satisfied are you with the skills that this program has taught you to manage your depression and anxiety?” (1 = “Not at all satisfied”; 9 = “Very satisfied”); “How confident would you be in recommending this treatment to a friend who experiences similar problems?” (1 = “Not at all confident”; 9 = “Very confident”); followed by two questions about difficulty with the program and requesting additional feedback, which will require free text responses.

### Data management

All data will be collected via the Virtual Clinic software and stored on the Virtual Clinic server. All information collected will be coded with a participant identification number to allow data-to-patient matching. Additional clinical material not obtained via the online application, mainly pertaining to data obtained via the diagnostic intake interview, will be collected and stored in written format in a secure location in CRUfAD. Any identifiable information will remain confidential, except as required by law. Only members of the site research team will have access to participant information and data in order to monitor patient progress. During data analysis, re-identifiable data (i.e. coded data) will be used. At study completion, non-identifiable data will be written to a password-protected database. All data will be extracted from the Virtual Clinic servers. Analysis will be conducted using Statistical Package for the Social Sciences (IBM SPSS, IBM Corp., Armonk, NY, USA).

Participants will be informed in writing that the research team plans to disseminate the trial results in peer-reviewed scientific publications and presentations. Participants are informed that in any such dissemination, their anonymity will be maintained. Participants will be sent (via email) a written summary of the results in lay terms following completion of the trial study phase.

